## Abstract

**Aim:**

The COLO‐COHORT study aims to produce a multi‐factorial risk prediction model for colorectal neoplasia that can be used to target colonoscopy to those at greatest risk of colorectal neoplasia, ensuring that people are not investigated unnecessarily and maximizing the use of limited endoscopy resources. The study will also explore the link between neoplasia and the human gut microbiome. Additionally, the study aims to generate a cohort of colonoscopy patients who are ‘research ready’ through the development of a consent‐for‐contact (C4C) platform, to facilitate a range of colorectal cancer prevention studies to be conducted at scale and speed.

**Methods and analysis:**

This is a multi‐centre observational study involving sites across the UK. Recruitment is over a 6‐year period (2019–2025). Patients recruited to the study are those attending for colonoscopy. Patients are recruited into two groups, namely observational group A (10 000 patients) and C4C group B (10 000 patients), known as COLO‐SPEED (Colorectal Cancer Screening Prevention Endoscopy and Early Diagnosis; https://colospeed.uk). Patients complete a health questionnaire, provide anthropometric measurements and submit biosamples (blood and stool—depending on the part of the study they are recruited into). Patients' colonoscopy and histology findings are also recorded. Models of factors associated with the presence of neoplasia at colonoscopy will be developed using logistic or multinomial regression. For internal validation, model discrimination and calibration will be assessed and bootstrapping and cross‐validation approaches used. To enable long‐term follow‐up for outcomes related to colorectal cancer and polyps, patients are asked to consent to follow‐up through data linkage with national databases.

**Dissemination:**

In keeping with good research practice, following analysis by the study team the study investigators will make the anonymized dataset available to other researchers. The C4C platform will also be accessible to other researchers. The study findings will be submitted for publication in peer‐reviewed journals and lay summaries will be disseminated to participants and the wider public.

## INTRODUCTION

Colorectal cancer (CRC) is the second most common cause of cancer death worldwide accounting for 935 000 deaths per year [1]. In the UK around 42 000 people are diagnosed with CRC annually with 16 000 dying from it [2]. The majority of CRCs develop through well‐established pathways with pre‐cancerous colorectal lesions (colorectal adenomas and serrated polyps) progressing to CRC [3, 4]. The process can take 10–15 years and there is therefore a window of opportunity for these lesions to be detected and removed during colonoscopy [5].

Advances in prevention, diagnosis and management have resulted in an improvement in the mortality from CRC over the past few decades. In the UK, the introduction of the Bowel Cancer Screening Programme (BCSP) has led to a stage shift in CRC diagnosis; however, the majority of CRCs in the UK are still diagnosed through symptomatic services rather than screening [6].

In the UK more than 675 000 colonoscopies are performed annually and the demand is rising [7]. Endoscopy services were already struggling to provide capacity to meet this demand and the COVID‐19 pandemic has significantly reduced endoscopy capacity [8, 9, 10, 11]. For patients, colonoscopy may provoke anxiety, has some risk associated and requires pre‐procedural bowel preparation, which patients find unpleasant [12]. To best utilize this limited resource and ensure that people are not investigated unnecessarily, we need to better identify those at greatest risk of CRC and target colonoscopy at those individuals.

At present, the BCSP relies on one factor, age, as the only criterion for eligibility for screening. In England, Wales and Northern Ireland, individuals between 56 and 74 years are invited to participate in each nation's respective bowel cancer screening programme, with plans to reduce the age threshold to 50 years. In Scotland, 50 years of age is already used as the threshold for invitation to their programme. For symptomatic patients, referral for colonoscopy is largely guided by symptoms or clinical suspicion but symptoms do not correlate well with the presence of colorectal neoplasia [13]. A wide range of risk factors for CRC have been identified including increasing age, male sex, obesity, alcohol intake, smoking, ingestion of red meat, family history and reduced physical activity [14, 15, 16, 17]. Currently, these risk factors are not taken into account when assessing whether or not an individual may require a colonoscopy.

Biomarkers could also be of value for patient stratification for investigation. Non‐invasive tests such as the faecal immunochemical test (FIT) have been used successfully in the screening setting and have recently been introduced into the English BCSP, with use in the symptomatic setting evolving [18]. Two large, published UK cohorts report good diagnostic performance of the FIT in low‐risk patients in primary care [19, 20]. As a consequence of the reduction in availability of lower gastrointestinal services due to the COVID‐19 pandemic, in some areas the FIT has been used to prioritize patients for definitive lower gastrointestinal investigation; however, the use of the FIT varies hugely nationally.

Additionally, the relationship between gut microbiota and health and disease has been increasingly studied. There is evidence that certain micro‐organisms, in particular the *Fusobacterium* species, are associated with colorectal neoplasia; however, most existing studies are small and knowledge as to whether the gut microbiota could help identify or alter the natural history of patients who harbour the potential for colorectal neoplasia remains somewhat limited [21, 22, 23, 24].

Risk stratification is a technique for systematically categorizing patients based on their risk of a particular condition. Managing patients based on their risk level may make better use of limited health service resources whilst also benefitting patients by avoiding the need for unnecessary investigations in those at low risk [25]. This approach has been utilized in other areas of healthcare, for example in cardiovascular disease, using the QRISK score to guide the need for therapeutic prevention of vascular events (such as myocardial infarction and stroke) and the FIB‐4 score within hepatology to non‐invasively stage an individual's risk of fibrosis [26, 27]. The potential for using risk prediction models to identify patients with colorectal neoplasia has been increasingly studied. Various risk prediction models have been developed in both the screening and symptomatic settings but model performance varies [25, 28, 29]. Further work needs to be undertaken to achieve a risk model with sufficiently good performance for prediction of colorectal neoplasia to justify use in clinical practice. We hypothesize that it is possible to develop a risk prediction model using clinical factors and readily available laboratory biomarkers (including the FIT) that will enable us to predict patients at highest risk of colorectal neoplasia. We also hypothesize that the stool microbiome in patients may be helpful in identifying those at greatest neoplasia risk [30].

Most current research strategies are based on answering a single question with the study ending with the recruitment of the final patient; however, current good research practice supports making datasets discoverable [31]. Furthermore, most patients for CRC research are recruited on a study‐by‐study basis, despite it being advantageous to be able to deliver multiple studies simultaneously. An alternative approach is to develop a pool of research‐ready patients who can be contacted when studies relating to an aspect of screening, prevention and early diagnosis research relevant to them becomes available. This research‐ready consent‐for‐contact (C4C) population would enable a range of CRC‐related studies to be conducted at scale and speed and would facilitate rapid engagement with patients and the public in the development and design of research studies.

The objectives of the COLO‐COHORT study are as follows:
to develop a multi‐factorial risk prediction model for prevalent colorectal neoplasia;to develop a cohort of patients who will be followed up long term through medical records and national databases for outcomes related to colorectal neoplasia, in order to test the long‐term value of the risk prediction model;to compare the structure and diversity of the faecal microbiome in patients with and without colorectal neoplasia;to develop a C4C platform of colonoscopy patients who have consented to be contacted for current and future research opportunities;to build a digital platform to support patient involvement, recruitment and data collection.

## METHODS AND ANALYSIS

### Study design

COLO‐COHORT is a multi‐centre observational study involving sites across the UK. Patients are recruited into two groups, namely group A and C4C group B, also called COLO‐SPEED (Colorectal Cancer Screening Prevention Endoscopy and Early Diagnosis; https://colospeed.uk). Recruitment will take place over a 6‐year period (2019–2025).

For group A, 10 000 patients will be recruited into the main observational element of the study. This group is subdivided into groups A1 and A2. Patients in group A1 submit blood and stool samples, whereas these samples are not required for patients in group A2; instead results from previous blood/stool tests are obtained from patient records.

For group B, 10 000 patients will be recruited into the C4C arm of the study (COLO‐SPEED). These patients may also be recruited into group A and/or into other endoscopy studies.

The study includes patients attending colonoscopy as part of the English BCSP and those referred through standard National Health Service (NHS) care for indications including, but not limited to, symptoms, family history or as part of surveillance programmes.

Groups A and B indicate what patients have consented to and are not defined to allow comparison between the groups.

### Study population: inclusion, exclusion and withdrawal criteria

Patients eligible for the study are those attending for a planned colonoscopy. Potential study participants are identified from outpatient clinics, endoscopy lists, pre‐assessment clinics or other clinical referral routes such as straight to test procedures depending upon how local services are configured. The approach to participant identification varies between sites due to variations in referral pathways to endoscopy and differing pre‐assessment approaches; therefore, where local pathways differ, these are incorporated.

#### Group A

##### Inclusion criteria

Aged ≥30 years and able to give informed consent (colorectal neoplasia is very rare in people below 30 years and this is why this age threshold was chosen);Patients attending colonoscopy:
through the BCSP (FIT positive, Bowelscope conversion, surveillance);through standard NHS care (most commonly referred due to iron deficiency anaemia, altered bowel habit, weight loss, rectal bleeding, planned polypectomy, on the basis of family history, abnormal cross‐sectional imaging, polyp surveillance or post CRC surveillance).

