##### Exclusion criteria

Unable to give informed consent;Known polyposis syndrome;Previous total colectomy;Known colonic stricture which would limit complete colonoscopy;Attending for planned therapeutic procedure other than polypectomy, such as insertion of colonic stent;Attending for assessment of known inflammatory bowel disease activity or for inflammatory bowel disease surveillance;Patients currently recruited into an interventional clinical trial of a medicinal product for CRC prevention.

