### Statistical analysis and sample size

Data from patients recruited to group A will be used to develop the risk prediction model. Primary analysis will be based on the outcome of the presence of colorectal neoplasia at the recruitment colonoscopy. This will be defined as the presence of advanced adenoma (AA)/CRC. AA will be defined as an adenoma of at least 10 mm in size or containing high‐grade dysplasia [38]. Secondary analyses will focus on other relevant outcomes, including CRC (only), AA (only), any adenoma, any polyp, serrated polyps, numbers of adenomas and number of polyps. The TRIPOD statement will be followed for reporting of the risk prediction model [39].

Initially we will develop models separately for BCSP and other (mainly symptomatic) subjects; further analysis will explore whether an overall model can be created. Firstly (in the non‐BCSP subjects), sensitivity, specificity, positive predictive value and negative predictive value of FIT alone for the detection of the presence of AA/CRC will be assessed. Different FIT cut‐offs will be explored. Subsequently, the relationship between patient characteristics and lifestyle, phenotypic information, FIT results, blood markers and presence of AA/CRC will be investigated using logistic regression. Backwards elimination of candidate predictors will be used to identify variables which best predict neoplasia [40]. Receiver operating curve plots, area under the curve analyses of sensitivity and specificity, and Harrell's C‐index will be used to characterize the discriminative ability of the models [41, 42]. Calibration will be assessed using Hosmer and Lemeshow tests, the percentage of people reclassified by different models and the net reclassification index [43]. Internal validation will be undertaken using bootstrapping to quantify the model's potential for overfitting and optimism in estimated model performance [40]. Cross‐validation approaches will also be applied, systematically excluding groups of subjects (e.g., by site) in turn [44]. In addition, multinomial, or ordinal, logistic regression will be used to investigate predictors of the secondary outcomes. Multiple adenomas may occur in an individual. It is anticipated that the presence of multiple adenomas will be zero‐inflated, with some patients having zero and others many. The extent to which zero‐inflated models (e.g., allowing for aggregation) improve the prediction of the presence of adenomas will be assessed.

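### Attenders for planned polypectomy, whose lesion is already identified, enter the primary AA/CRC model and the FIT-alone accuracy analysis although they lie outside the population the model is meant to triage

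*Protocol article*

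**What the plan says.** Under Group A, Inclusion criteria, the standard NHS care route names its commonest referral reasons, among them "weight loss, rectal bleeding, planned polypectomy, on the basis of family history". Under Group A, Exclusion criteria, one item reads "Attending for planned therapeutic procedure other than polypectomy, such as insertion of colonic stent". Planned polypectomy is therefore eligible by intention, not by oversight.

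Under Statistical analysis and sample size, the development population is stated without restriction by indication: "Data from patients recruited to group A will be used to develop the risk prediction model". The outcome is fixed to the same examination: "Primary analysis will be based on the outcome of the presence of colorectal neoplasia at the recruitment colonoscopy". It is AA or CRC, with size and dysplasia criteria for AA ("AA will be defined as an adenoma of at least 10 mm in size or containing high"-grade dysplasia). The only initial split is "Initially we will develop models separately for BCSP and other (mainly symptomatic) subjects". Planned polypectomy is listed under standard care, so it falls in the second stratum. That stratum is also where the sensitivity, specificity, "positive predictive value and negative predictive value of FIT alone for the detection of the presence of AA/CRC will be assessed".

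The Abstract and Introduction give the purpose: to direct colonoscopy to people at greatest risk and spare others an unnecessary examination.

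**The concern.** A diagnostic or triage model should be developed in people for whom the decision is still open. Someone attending to have a known polyp removed is not one of them: the lesion was found earlier and is the reason for the visit. For these patients the outcome at the recruitment colonoscopy is in good part settled at entry.

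A small number of such patients can supply a large share of the events. Those events set the model intercept, and so every absolute risk that would later be compared with a referral threshold. They also weigh in the backward elimination of predictors and in the FIT cut-off exploration. The planned bootstrap and leave-site-out validation would not correct this, because known-lesion patients stay in the data being resampled. A bootstrap reproduces the same mix, and leaving out a site removes only that site's patients.

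**Working it through.** The plan gives no figure on this point to reproduce: no share of planned-polypectomy patients, no AA/CRC prevalence, no FIT accuracy. Every numerical input below is an assumption, and the structure comes from the sections cited above.

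**1. Prevalence and share of cases.** Let f be the planned-polypectomy share of non-BCSP attenders, q the proportion of them with AA/CRC, and p the proportion in all other non-BCSP attenders.

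- Prevalence = f·q + (1 − f)·p
- Share of cases already identified = f·q / [f·q + (1 − f)·p]

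| f | q | p | Prevalence | Share of cases |
|---|---|---|---|---|
| 2% | 40% | 8% | 0.008 + 0.0784 = 8.6% | 0.008/0.0864 = 9% |
| 5% | 60% | 8% | 0.030 + 0.076 = 10.6% | 0.030/0.106 = 28% |
| 10% | 80% | 8% | 0.080 + 0.072 = 15.2% | 0.080/0.152 = 53% |

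**2. FIT alone.** Assume sensitivity 60% and specificity 80% in diagnostic attenders, and the same specificity in polypectomy attenders without AA/CRC. Let s be FIT sensitivity for the known lesions.

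Without polypectomy attenders (p = 8%):
- PPV = 0.048/(0.048 + 0.184) = 20.7%
- NPV = 0.736/(0.736 + 0.032) = 95.8%

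With f = 5% and q = 60%, true positives = 0.0456 + 0.03·s, false positives = 0.894 × 0.2 = 0.1788, and true negatives = 0.7152:

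| s | Sensitivity | PPV | NPV | Single-cut-off AUC = (sens + spec)/2 |
|---|---|---|---|---|
| 30% | 51.5% | 23.4% | 93.3% | 0.658 |
| 60% | 60.0% | 26.2% | 94.4% | 0.700 |
| 80% | 65.7% | 28.0% | 95.2% | 0.728 |

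The AUC without these patients is (0.60 + 0.80)/2 = 0.700. PPV rises and NPV falls in every row. The same holds over f = 2-10%, q = 60-80%, s = 30-80%, with p at 8% or 12%.

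The NPV result has a limit. At q = 60%, NPV falls as long as (1 − s)·0.6/(0.4 × 0.8) exceeds 0.032/0.736 = 0.0435, that is, for s below about 98%. At q = 40% the same calculation gives about 95%.

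Sensitivity and AUC fall, stay put or rise according to whether s is below, equal to or above 60%.

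**3. Discrimination of the multivariable model.** A simulation used 400,000 patients, a linear predictor with SD 0.9 and base prevalence 8%, which gives AUC 0.73 without polypectomy attenders. Adding them at f = 5%, q = 60% gives:
- 0.79 if some predictor identifies them;
- 0.70 if none does and the predictors act in them as in everyone else;
- 0.67 if none does and the predictors are unrelated to outcome in them.

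The sign depends on information the article does not give.

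**The case against.** Four points can fairly be made against this.

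**The analysis set belongs in the SAP.** The article promises a full SAP before analysis, and eligibility for a multi-purpose cohort need not equal the model-development set. That is true in general, and the unseen SAP may deal with it. But the article itself names group A as the development data and BCSP versus other as the split. Followed as written, that puts known lesions into the primary model.

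**Not every planned polypectomy is a case.** Lesions under 10 mm without high-grade dysplasia do not meet the AA definition. This stands: the outcome is partly rather than wholly known, which is why q runs from 40% to 80% above and not to 100%.

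**Discrimination.** A reader might infer that including these patients must inflate the AUC. The documents do not support that. Referral indication is not among the named candidate predictors (patient characteristics, lifestyle, phenotype, FIT, blood markers). Medical history is collected, so polyp history could act as a partial proxy, but the article does not say that it is a candidate. Likewise one might infer that both FIT predictive values are inflated. Higher prevalence raises PPV but generally lowers NPV, which for a rule-out test is the conservative direction.

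**Surveillance.** A reader might extend the point to polyp and post-CRC surveillance patients and ask for a separate stratum. Their earlier lesions have been removed, the outcome is not known beforehand, and the article names surveillance as part of the study population. A separate stratum would be a preference, not the correction of an error.

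**Conclusion.** The point holds in this form: by its own eligibility and analysis text, the plan places patients with an already identified lesion in the primary non-BCSP model and in the FIT-accuracy analysis, at odds with its triage purpose.

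The direction is clear for prevalence, absolute risk and PPV (up), given only that AA/CRC is commoner in these patients than in diagnostic attenders and that FIT is not almost blind to their lesions. It is clear for NPV (down) unless FIT detects nearly all known lesions. It is open for FIT sensitivity and for discrimination.

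The size cannot be derived from the article. The range of 9-53% of cases rests wholly on the assumed share, yield and base prevalence. It shows that the effect could be minor or dominant, and that the study's own referral-reason data will have to settle which. This should be corrected before the analysis is fixed. It does not affect recruitment or the validity of the cohort for its other aims.

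**What to change.** State in the statistical section, and carry into the SAP, that the primary non-BCSP model-development set and the FIT-alone accuracy set are group A patients excluding those attending for planned polypectomy of a known lesion, identified from the referral reason. Report a sensitivity analysis that adds them back, and give their number and their AA/CRC yield so that readers can judge the influence. Keep these patients in the cohort for long-term follow-up, microbiome work and consent-for-contact.

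The cost is a few lines of text and a small loss of records for model development. The loss of events could be proportionately larger (28% in the central assumed case), so the events-per-candidate-predictor count should be rechecked on the reduced set. Recruitment and data collection need not change, provided the referral reason is held for each patient. The eligibility criteria are framed by it, but the article does not list it among the group A data items.

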##### Exclusion criteria

Unable to give informed consent;Known polyposis syndrome;Previous total colectomy;Known colonic stricture which would limit complete colonoscopy;Attending for planned therapeutic procedure other than polypectomy, such as insertion of colonic stent;Attending for assessment of known inflammatory bowel disease activity or for inflammatory bowel disease surveillance;Patients currently recruited into an interventional clinical trial of a medicinal product for CRC prevention.

#### Group B

The COLO‐SPEED funding infrastructure is currently only available to sites that are part of the Northern Region Endoscopy Group (NREG.org.uk) and thus only patients from the northeast of England can be recruited into group B.

##### Inclusion criteria

Any patient attending for colonoscopy and able to give informed consent;≥18 years old;Patient attending for colonoscopy in a site supported by COLO‐SPEED infrastructure.

